#### Data processing and annotation

The acquired voice data will be converted into text information using speech recognition technology developed by the research group and will be compensated manually; annotations, such as pauses, fillers, nods, interjections, repetitions, co-supplementation, lexical responses, incomplete sentences, misstatements, etc., will also be made. We will mask the part of personal identifiers such as names when converting voice data into text information. At the same time, the following phonic information will be extracted from the recorded audio data to utilize the physical properties of the audio data in the machine learning model: fundamental frequency (F0); first, second, and third formant frequencies (F1, F2, F3); cepstral peak prominence (CPP); and Mel-frequency cepstrum coefficients (MFCC). These are the major features in speech-language analysis (40). Software such as Praat (41) and openSMILE (42) will be used to extract such phonic information.

Based on the annotated text data thus obtained, various variables are calculated using NLP techniques, such as morphological and syntactic analyses using MeCab (43, 44) and JUMAN (45, 46). For instance, these analyses will include the frequency of the occurrence of each part of speech, vocabulary (negative and positive words), syntactic complexity, length of the utterance, frequency of occurrence of person, use of pronouns and distance to the referent, use of case structure (“te, ni, wo, ha”), and so on. We will use NLP techniques to represent textual data as n-grams and word embeddings obtained from pre-trained models such as BERT (47).

Linguistic features considered to be characteristic of specific psychiatric diseases will be selected and statistically compared between groups (e.g., patients vs. healthy subjects, patients in different disease groups). This step is necessary to verify whether each variable has pathological validity before using it for machine learning.

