**Aim:**

The purposes of this study are to create a large dataset of Japanese speech data labeled with detailed information on psychiatric disorders and neurocognitive disorders to quantify the linguistic features of those disorders using natural language processing and, finally, to develop objective and easy-to-use biomarkers for diagnosing and assessing the severity of them.

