### Machine learning

The machine learning models in this study will be trained to perform the following tasks: (1) to predict whether a subject has or does not have psychiatric disorders such as depression, bipolar disorder, anxiety disorder, schizophrenia, or dementia; (2) to predict the severity of a subject's state based on the results of rating scales such as the Hamilton Rating Scale for Depression (HAM-D), the Young Mania Rating Scale (YMRS) for bipolar disorder, the Positive And Negative Syndrome Scale (PANSS) for schizophrenia, and MMSE for dementia; (3) to predict the improvement or deterioration of a subject's disorder with respect to a previously recorded state if the subject has undergone a prior assessment; and 4) to predict the scores of individual items in clinical rating scales that are indicators of different aspects of a subject's disorder, such as positive symptoms, negative symptoms, and disorganized symptoms for schizophrenia. The data used to train these machine learning models may include voice features extracted from voice data obtained from subjects, conversational and linguistic information from transcribed text data, and annotations assigned to the data described above.

Next, we will need to perform feature engineering and design the architecture of machine learning. The data, represented through NLP techniques, together with the features obtained through feature engineering processes, will be then used to extract disease features. In particular, disease features extraction will be performed relying on machine learning models such as decision trees, support vector machines (SVM), and deep learning architectures. Each model will be evaluated using cross-validation and then the relative importance of each feature will be estimated using a feature importance estimation method such as XGBoost. We will then evaluate the results using the mean absolute error, coefficient of determination, and correlation coefficients. We also plan to verify whether the features obtained in this manner can distinguish firstly between a normal and disease state, secondly among different diseases, and whether they can distinguish changes in disease severity over time.

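### Performance of models that use linguistic features will be estimated on manually corrected, annotated transcripts, although the final aim is an objective biomarker that is easy to use

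*Protocol article*

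**What the plan says.** The Aim in the abstract of the Protocol article ends with the intention to "develop objective and easy-to-use biomarkers for diagnosing and assessing the severity of them".

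The section Data processing and annotation describes two routes from the recording to the model inputs.

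- **Text route.** The voice data are "converted into text information using speech recognition technology developed by the research group and will be compensated manually". In addition, "annotations, such as pauses, fillers, nods, interjections, repetitions, co-supplementation, lexical responses, incomplete sentences, misstatements, etc., will also be made". The text features come from this product: "Based on the annotated text data thus obtained, various variables are calculated using NLP techniques".
- **Acoustic route.** Separately, "the following phonic information will be extracted from the recorded audio data to utilize the physical properties of the audio data". This covers F0, F1–F3, CPP and MFCC, and "Software such as Praat (41) and openSMILE (42) will be used to extract such phonic information".

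The Machine learning section says that the training data may include voice features, "conversational and linguistic information from transcribed text data, and annotations assigned to the data described above". The models are evaluated by cross-validation. No evaluation on recogniser output before manual correction is described.

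**The concern.** The Introduction and abstract motivate the study by the dependence of psychiatric judgement on the individual clinician, and the aim is a marker that is objective and easy to use. A person who corrects each transcript, and probably annotates it, is a human step inside the measurement. If that step is needed to reach the reported performance, the result belongs to a labour-intensive procedure. If it is not needed, the study would gain by showing so. As described, the evaluation cannot tell these two cases apart.

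Linguistic features are central to the study. The pilot classifier in the Sample size section used part-of-speech information and feature vectors from a language-processing package, and the pilot feature list includes morphemes, particles and fillers. Such counts depend on transcript quality.

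The Discussion notes that spoken data tend to be broken or ill-formed and that Japanese word boundaries are unclear. Recognition errors could plausibly differ between diagnoses, and the comparison between diseases would then be affected as well as the overall level. The documents give no error rates, so this is an inference.

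**Working it through.** **Step 1: follow each type of input through the plan.**

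| Model input | Source in the article | Passes through manual correction? |
|---|---|---|
| Text variables (parts of speech, vocabulary, syntax, n-grams, embeddings) | Corrected and annotated text | Yes |
| Annotations used as inputs | Added to the transcript; by hand or by software is not stated | Probably a human step (see below) |
| F0, F1–F3, CPP, MFCC | Recording, by Praat or openSMILE | No |

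On the second row, the word for manual work is attached to the correction. The Discussion, however, treats a similar annotation protocol among examiners as essential, which makes human annotation likely.

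**Step 2: ask what cross-validation can show.** In every fold the training and held-out records have been processed in the same way. For a model that uses text variables, both sides hold corrected text. The estimate is therefore performance given correction. The effect of removing correction does not appear in it. The inter-rater check planned in the Discussion measures agreement between people, not performance without them.

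**Step 3: look for a figure in the plan.** There is none on this point. The pilot accuracy (72–80%, 30 participants, leave-one-out cross-validation) and the 90% target are given, but no recognition error rate and no accuracy on uncorrected text. The loss or gain cannot be computed from the documents.

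**Step 4: illustrate under an assumption.** Suppose an equal-variance binormal classifier, and suppose that leaving the text uncorrected adds noise unrelated to diagnosis, so that the reliability of the score falls to L. Then

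accuracy on uncorrected text = Φ(√L × z(accuracy on corrected text)).

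For example, at 90% and L = 0.5: z(0.90) = 1.282; 1.282 × 0.707 = 0.906; Φ(0.906) = 0.818.

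| Accuracy on corrected text | L = 0.9 | L = 0.7 | L = 0.5 |
|---|---|---|---|
| 90% (target) | 88.8% | 85.8% | 81.8% |
| 80% (pilot, upper) | 78.8% | 75.9% | 72.4% |
| 72% (pilot, lower) | 71.0% | 68.7% | 66.0% |

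The smallest drop is 72 − 71.0 = 1.0 point and the largest is 90 − 81.8 = 8.2 points. The values of L are assumed, and the range depends on them entirely.

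**Step 5: test the assumption.** If recognition errors differ by diagnosis, the noise is not unrelated to diagnosis and the formula does not apply. Differential errors could reduce the separation between groups, or could raise it because the errors themselves carry information about the group. The table therefore shows what one mechanism would do. It does not estimate the effect or fix its sign.

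**The case against.** The strongest reply is that a stated processing choice is being read against a promise that the article does not make. Four parts of it deserve an answer.

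- **Not every input is corrected text.** This stands. Acoustic features come from the audio by software, and the list of training inputs is permissive. A reader might infer that performance will be measured only on hand-corrected, hand-annotated transcripts. The documents do not support that: acoustic-only models are possible under the plan, and hand annotation is likely but not stated.
- **No fully automatic tool is promised.** This also stands. Ease of use is not defined, and the biomarker is the last step after building the dataset and quantifying features. A reader might conclude that the reported figures do not describe the tool the study promises, but that goes beyond the text. What remains is that a human correction step sits poorly with an aim of objectivity and ease of use, and should be visible when performance is reported.
- **A condensed article may leave a secondary evaluation to the full protocol.** This is true of the missing run on uncorrected text, which is not an error by itself. It does not cover the source of the text variables, which the article states positively.
- **The magnitude rests on assumed inputs, and the cost is not zero.** Both are correct. A claim that automatic performance will be lower, or that particular features will be lost altogether, cannot be made from the documents. The article does not say that raw recogniser output is kept, more than 1,000 records existed by September 2022, and identifiers are masked during conversion to text. The fix has to deal with each of these.

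Correcting transcripts before testing whether features have pathological validity is a defensible choice at the dataset-building stage, and nothing here asks for it to be dropped.

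**Conclusion.** The point holds in a limited form. For models that use linguistic features, the planned performance estimates describe a pipeline with manual correction, and they carry over to automatic use only if removing that step makes little difference. Models that use only acoustic features are unaffected.

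The documents determine neither the size nor the direction of the difference. The drop of about 1 to 8 accuracy points is conditional on a binormal model, on reliability of 0.5 to 0.9 and on errors unrelated to diagnosis; none of these comes from the article. No passage contradicts another. This is a cheap improvement that would let the study answer its own aim more directly. It is not a design fault that invalidates the planned results.

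**What to change.** 1. Keep the raw recogniser output from now on. For existing records where it was not kept, regenerate it from the stored audio. Apply the same masking of identifiers as for the corrected text.
2. Re-evaluate the final models in the same folds on (a) uncorrected transcripts plus automatically extracted acoustic features, and (b) acoustic features alone. Say whether the models are refitted to the uncorrected text or only scored on it, because these answer different questions.
3. Report the difference from the corrected-transcript result overall and by diagnosis.
4. Label results from corrected transcripts as such, and rest any conclusion about ease of use on the automatic version.

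The cost is computation: rerunning the recogniser where needed, recalculating the text variables and repeating the evaluation of the final models, with masking to be applied to the uncorrected text. No new participants are required. The headline figure for the automatic version may be less favourable.

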In the pilot study, we used 62-dimensional features for speech information and linguistic information. These features include linguistic features such as the number of morphemes, the number of vocabulary, the number of nouns, verbs, and adjectives, the number of particles “ga” etc., and the number of conjunction, and non-linguistic features such as the total time, the response time, the number of fillers, the formants. In the present study, we plan to use a total of about 100 independent variables for the analysis. We will also be employing dimension reduction and feature selection techniques to reduce the number of independent variables in the model. Based on the approximations, we estimate that the desired sample size is approximately 1,000. It should also be noted that the actual needed number of samples is likely to be lower.

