The challenges of this research are as follows: the difficulty of keeping inter-rater reliability high, the scarcity of previous or similar studies, findings, and datasets in the Japanese-speaking region, and the peculiarity of the Japanese language. First, it will be essential to ensure a similar annotation protocol among the examiners. Similarly, it will be very important to keep the inter-rater reliability high when diagnosing and/or assessing patients. Anticipating this issue, the study team has developed educational modules to maintain a high quality of ratings, and the inter-rater reliability will be tested using random sampling during the study period. Second, as far as we know, this is the first study of this kind to be conducted on such a large sample size in a Japanese-speaking region. The quantity of publicly available conversational data in the Japanese language is relatively small, and almost none is from speakers with mental disorders. To date, most of the reported cases of NLP applied to psychiatric disorders have been conducted in English-speaking areas; therefore, it might be difficult to replicate the findings of the previous studies directly in this study. Finally, we discuss the linguistic characteristics of the Japanese language. Some features cannot exist in Japanese due to differences in grammar. For example, the determiners used to analyze linguistic features of psychosis (37) do not exist in Japanese. Secondly, the Japanese language is agglutinative in that it does not use spaces between words, so its word boundaries are not as clear as they are in other languages. Another challenge involves handling spoken conversational data, which tends to be broken or ill-formed. Furthermore, the Japanese language has the characteristic of often omitting arguments such as subjects. At the same time, however, if common features capable of identifying specific psychiatric disorders across languages can be found, such information would likely become an important disease feature. Although there are many challenges, this research will enable us to study the languages of psychiatric disorders statistically and comprehensively, and it will provide a new interpretation of language to psychiatrists.

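### Transcripts are hand-corrected and annotated with no stated masking to diagnosis, so annotator expectation could enter the text-based predictors undetected

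*Protocol article*

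**What the plan says.** Under Data processing and annotation, recordings go through the research group's speech recognition. The output "will be compensated manually; annotations, such as pauses, fillers, nods, interjections, repetitions, co-supplementation, lexical responses, incomplete sentences, misstatements, etc., will also be made". The sentence does not name who does this. The one pointer is in the Discussion, where "it will be essential to ensure a similar annotation protocol among the examiners"; the role of examiner is not defined.

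The coded text then feeds the analysis: "Based on the annotated text data thus obtained, various variables are calculated using NLP techniques". The Machine learning section adds: "The data used to train these machine learning models may include voice features extracted from voice data obtained from subjects", and continues with "conversational and linguistic information from transcribed text data, and annotations assigned to the data described above". The Sample size section lists, among the 62 pilot features, "non-linguistic features such as the total time, the response time, the number of fillers, the formants"; fillers are one of the hand-annotated event types.

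On masking, the Data collection and Data processing sections describe study numbers and the removal of names and similar identifiers from the text. Nothing is said about hiding diagnosis or severity from annotators. On quality control, the Discussion describes training modules aimed at rating quality and a reliability test on a random sample.

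**The concern.** Deciding whether a sentence is incomplete, a word is a misstatement or an utterance is a repetition takes judgement. Someone who believes the speaker has schizophrenia or dementia may mark more of such events than someone who believes the speaker is a healthy volunteer. If those marks become predictors and the target is the diagnosis, the model can partly learn the annotator's belief.

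This bears directly on the aim. The study wants an objective marker because, as the Introduction argues, diagnosis rests too much on the individual psychiatrist's sensitivity and experience. Expectation entering through the coding would put some of that judgement back into the predictors. Apparent accuracy could then exceed what fully automatic or masked transcription would deliver.

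**Working it through.** No figure in the document bears on this point, so the check sets the sections side by side.

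1. **Is there human judgement upstream of the predictors?** Yes. Correction and annotation are manual, and variables are calculated from the annotated text without qualification. Annotations as direct inputs are permitted, not fixed. The filler count shows that one annotated item was already used as a feature.

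2. **Can the annotator tell the group?** Usually. The Conversation data section has the free conversation cover how the illness has developed and the patient's present state. Removing names does not hide that. This holds even if the annotator never met the participant. The picture-description and story-telling tasks do not ask about the illness.

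3. **Can the annotator tell the rating or the visit?** Not shown. A transcript may reveal illness, but it does not reveal a HAM-D, PANSS or MMSE score.

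4. **Which predictors are exposed?** Those that depend on annotations or corrected text. F0, formants, CPP and MFCC are extracted from the audio by software and are not exposed.

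5. **Would the planned checks reveal the bias?**
   - *Cross-validation:* training and held-out records are coded in the same way, so a bias is present in both and counts as signal.
   - *Reliability test:* it follows a sentence on diagnosing and assessing patients, so it may not cover annotation. If it does, two annotators who both infer the diagnosis can agree and share the bias. The Introduction itself says that psychiatrists hold a common view of these features.
   - *Group comparison before modelling:* features thought characteristic of a disorder are compared between groups to confirm their validity. Expectation would move them in the expected direction, so this step would tend to pass them.

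6. **How large could it be?** The following is illustration only, because every shift is assumed. With no true difference and normal features, a coding shift of d standard deviations gives AUC = Φ(d/√2):
   - One feature, d = 0.2: Φ(0.141) = 0.556. With d = 0.5: Φ(0.354) = 0.638.
   - Nine named annotation types, all shifted the same way and independent: the sum shifts by 9d with SD √9 = 3, so the effective shift is 3d. For d = 0.1, Φ(0.3/√2) = 0.584; for d = 0.2, Φ(0.6/√2) = 0.664.
   - The same nine with an assumed pairwise correlation of 0.3: variance 9 + 72 × 0.3 = 30.6, SD 5.53, effective shift 9d/5.53 = 1.63d. For d = 0.1, AUC is about 0.55; for d = 0.2, about 0.59.

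   The result depends heavily on the assumed shift, the correlation and a common direction. A common direction is doubtful across disorders whose speech differs in kind.

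**The case against.** A reader might infer from the word examiners that each transcript is coded by the person who interviewed and rated that participant, and so by someone who knows the diagnosis, the visit and the score. The document does not support that. The term is undefined, interviewers and raters are named differently elsewhere, and the Discussion treats annotation and rating in separate sentences. Nor does it say that annotations will certainly be model inputs, or that accuracy is inflated.

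It can also be argued that a journal article leaves annotator identity and masking to an annotation manual, so that silence is no finding. Silence alone would indeed not suffice. The point rests on the workflow that is stated: the recorded content discloses the illness, people code that content, and the code feeds the predictors. Unless something not described intervenes, group is visible during coding.

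Further limits stand. The AUC figures are not evidence of bias. Acoustic features are unaffected, and part-of-speech counts, n-grams and embeddings are computed by tools, so they are exposed only through the corrected or annotated text. More than 1,000 records had been collected by September 2022, so masking from now on may miss much of the data.

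**Conclusion.** The concern holds in a limited form. As the workflow is described, annotators will usually be able to infer patient or healthy status, and often the disorder, while coding text that supplies predictors. Expectation could therefore enter the text-based features, and none of the described checks would show it. Knowledge of scale scores or visit, and identity of annotator with interviewer or rater, are not established.

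The size cannot be estimated from the document, and the bias may be negligible. The conclusion assumes that annotators work through the free conversation as recorded and that no masking exists beyond removal of identifiers. If masking is already in place, one sentence saying so, and how it works for free conversation, largely answers the point. Otherwise it should be addressed before performance is presented as that of an objective marker.

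**What to change.** 1. Report model performance from uncorrected automatic transcripts and from acoustic features beside the result from corrected and annotated text. The study already produces both. Similar performance would be reassuring. A gap would not prove bias, since correction also removes recognition errors, but it would show how much rests on manual coding.

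2. Report performance separately for the picture-description and story-telling segments, which do not ask about the illness. This protects best where those segments are cut out and coded apart from the free conversation.

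3. For remaining files, have existing annotators work on recoded files, in mixed order, from participants they did not interview or rate, with diagnosis and scale scores withheld.

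The cost is some file handling and extra analysis, with no new visits or participants. The article gives no annotation staffing, so the effect on workload cannot be judged from it. Masking will remain imperfect for free conversation, and step 3 does nothing for files already annotated; for those, steps 1 and 2 are the available check.

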### Sample size

The results of a pilot study conducted on 30 participants prior to the main study showed that the combined NLP and machine learning had an accuracy of 72–80% for binary classification to differentiate between disease and healthy controls (based on a leave-one-out cross-validation). The demographic data in the pilot study are as follows. Age (years, mean ± SD): 56.8 ± 16.9, Gender (%male): 46.7, Diagnosis: 5 schizophrenia, 1 bipolar disorder, 4 depression, 5 anxiety disorder, 5 neurocognitive disorder, and 10 healthy controls.

Specifically, we used the part of speech information as well as feature vectors extracted from the data points using an NLP package called SpaCy as the input to train an XGBoost model for predicting the labels of the data points. We cross-validated the XGBoost model using leave-one-out cross-validation (LOOCV) where we would leave one data point as the test data and train an XGBoost model using the remaining data points. The process repeated for each data point and computed the accuracy of the LOOCV as the ratio of correctly predicted data points out of all of the data points. We further optimized the hyperparameters of the XGBoost model by choosing the set of parameters that has the highest LOOCV accuracy.

We constructed a learning curve to estimate the number of samples required to achieve a classification accuracy of 90%. Starting from a sample size of 15, we randomly sample 15 data points from the total of 30 data points and perform the LOOCV as described above, and repeat the random sampling of 15 data points 10 times, each time keeping track the optimal classification accuracy to get an idea of the distribution of the accuracy for 15 data points.

We then repeat the whole process at one-sample increments until we reach 29 samples. The resulting accuracies are then fitted to a linear model. Based on the parameters of the fitted linear model, we estimated the number of data points required to achieve an accuracy of 90%.

We calculated that a minimum of 50 samples would be required. In addition, considering the variability of the data over a wide range of age groups, severity of illness, and regional differences, it was estimated that about 10 times the number of samples would be necessary. Another means of approximating sample sizes for regression analysis is that the number of cases should be approximately 10 times the number of the independent variables used to obtain statistical confidence (48).

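### A between-group check on each variable is placed before machine learning; unless it is kept inside the training folds, cross-validated diagnostic performance will be too high

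*Protocol article*

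**What the plan says.** The Data processing and annotation section of the protocol article states: "Linguistic features considered to be characteristic of specific psychiatric diseases will be selected and statistically compared between groups". Its examples are patients against healthy subjects and one disease group against another. The reason given is "This step is necessary to verify whether each variable has pathological validity before using it for machine learning".

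The Machine learning section lists four tasks. The first is "to predict whether a subject has or does not have psychiatric disorders such as depression, bipolar disorder, anxiety disorder, schizophrenia, or dementia", which is the label used in the comparison. The others concern severity, change since an earlier assessment, and individual rating-scale items. On evaluation it says "Each model will be evaluated using cross-validation and then the relative importance of each feature will be estimated". It adds "We also plan to verify whether the features obtained in this manner can distinguish firstly between a normal and disease state", and then names the distinction among diseases and change in severity.

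The Sample size section says "we plan to use a total of about 100 independent variables for the analysis", and also "We will also be employing dimension reduction and feature selection techniques to reduce the number of independent variables in the model". It does not place that selection relative to the folds. No section describes a hold-out set, an external test set or nested cross-validation.

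**The concern.** Cross-validation is honest only if nothing about the test fold's outcome has entered the model, and that includes the choice of its inputs. A comparison of diagnostic groups uses the outcome. If it decides which variables go forward, and it was run on participants who later form the test folds, each test fold has already helped to pick variables that separate its own members. The classifier then does better than chance even when no variable carries information.

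The study aims at objective markers for diagnosing and grading these disorders, so discrimination between patients and healthy subjects, and between diseases, is a main output. Optimism there would make weak features look usable and would put chance findings among those reported as disease features.

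The article gives some reason not to leave the order to good practice. In the Sample size section, the pilot hyperparameters were chosen by the same leave-one-out accuracy that was used to assess the model.

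**Working it through.** **The plan's own figure.** The Sample size section uses the rule "the number of cases should be approximately 10 times the number of the independent variables used to obtain statistical confidence". With about 100 variables, 10 × 100 = 1,000, which reproduces the stated desired sample size. This confirms about 100 as the number of candidate variables. The article gives no screening threshold, so there is no stated error rate to reproduce.

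**Inputs from the article.**
- Candidates: about 100 (Sample size).
- Group sizes in September 2022 (Discussion): schizophrenia 102, depression 89, bipolar disorder 58, anxiety disorder 35, neurocognitive disorder 79. The sum is 102 + 89 + 58 + 35 + 79 = 363. With more than 400 participants, this leaves more than 400 − 363 = 37 healthy controls.

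**Assumptions.** Screen by two-sided t-test at p<0.05; one record per participant; normally distributed variables; a linear discriminant; stratified 10-fold cross-validation; 40 healthy controls where a control group is needed.

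**Step 1: expected chance passes in one contrast.** With no informative variable, 100 × 0.05 = 5 variables pass. The simulation kept 4.9 to 5.2 on average.

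**Step 2: AUC with no informative variable.** "Outside" means one screen on all records before cross-validation. "Inside" means the screen is repeated in each training fold. Correlation is within blocks of 10 variables.

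| Variables | 35 vs 58, outside | 102 vs 89, outside |
|---|---|---|
| 100, independent | 0.73 to 0.75 | 0.66 to 0.68 |
| 100, correlation 0.5 | 0.68 | 0.62 |
| 100, correlation 0.8 | 0.60 | 0.57 |
| 20, independent | 0.60 to 0.64 | 0.56 to 0.59 |
| 20, correlation 0.5 | 0.55 | 0.54 |

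Screening inside the folds gave about 0.50 (single runs 0.48 to 0.53). A repeat run moved cells in the lower rows by a few hundredths, at most 0.07 and upward, without changing the pattern.

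**Step 3: balanced accuracy (correct value 0.50), 100 independent noise variables.**
- 35 vs 40: 0.69 outside, 0.50 inside.
- 102 vs 40: 0.66 and 0.50.
- 102 vs 89: 0.63 and 0.50.
- 363 vs 40: 0.64 and 0.50.
- 500 vs 500: 0.55 and 0.50. The bias shrinks as both groups grow but does not vanish.

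**Step 4: some real signal.** With 10 of 100 variables separated by 0.5 standard deviations, balanced accuracy is 0.78 outside and 0.70 inside (102 vs 40), and 0.79 and 0.72 (363 vs 40). The optimism is then about 0.07 to 0.08.

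**The case against.** The strongest reply is that the article does not say what the criticism needs. It does not say which records are compared, gives no p-value or effect-size rule, and never says that a failing variable is dropped. A check of pathological validity could be one of clinical plausibility. The features are described as those considered characteristic of a disease, which suggests a first choice from known psychopathology, and that choice uses no labels. A condensed article may also leave the placement of selection within folds to a fuller plan.

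Much of this stands, and it makes the conclusion conditional. It does not remove the point. The article fixes an order (before modelling), a unit (each variable) and a purpose (verification before use), and calls the step necessary. A check that no variable could fail would not be necessary, so a filter is the natural reading. Prior choice of candidates reduces the bias, but the 20-variable rows show that it remains if a label-based check follows.

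A reader might infer more than the document supports:
- That the cross-validation is already known to be contaminated by a full-data screen. Use of the full data is an inference from silence.
- That the bias is far larger because n-grams and embeddings pass through the same screen. These are described separately, as representations of text. The comparison is confined to characteristic linguistic features, and the total planned is about 100 variables.
- That chance passes should be added up over all pairs of diagnostic groups. Those contrasts would not feed one model, and the article does not say that every variable is tested in every contrast.
- That all four tasks are compromised. A screen on diagnosis does not directly leak severity, change or item scores.
- That the later verification sentence and the further feature selection are errors in themselves. Neither says which data are used.

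**Conclusion.** The concern holds in conditional form. The stated sequence is a label-based check of each variable before use, followed by cross-validation on the same label, with no separation of data described. If the check filters inputs on records later used as test folds, performance on the diagnostic task and on the disease-against-disease distinction is biased upward.

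With pure noise, the AUC is about 0.67 to 0.75 for 100 independent variables at the two pairs of group sizes examined, and about 0.54 to 0.68 with correlated or about 20 pre-chosen variables, against about 0.50 when screening is inside the folds. These sizes rest on the assumed threshold, correlation, number of variables and classifier. Word and part-of-speech counts are likely to be correlated, so the independent case lies at the upper end. The direction of the bias does not depend on these choices.

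**What to change.** In Data processing and annotation, state whether the group comparison decides which variables enter the models. Then take one of two routes, and word the Machine learning and Sample size sections to match.

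1. Carry out any label-based screening, supervised dimension reduction and feature selection inside each training fold. Split folds by participant, since each contributes two to five assessments.
2. Fix the input list beforehand from prior psychopathology, without looking at labels. Keep the full-sample group comparisons as a descriptive result that does not choose model inputs. Any further label-based selection still belongs inside the folds.

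The cost is a change of wording, more computing under the first route, and reported performance that will look less favourable.
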